### Study objective and hypothesis

2.1

The primary aim of this study is to evaluate and compare the efficacy and safety of a 4-step egg ladder (4-EL) and a 5-step egg ladder (5-EL) in children diagnosed with IgE-mediated hen's egg protein allergy.

We hypothesize that the 4-EL, with 6-week intervals, will be sufficient for assessing tolerance to hen's egg proteins in children with IgE-mediated allergy and will result in a greater proportion of children achieving tolerance to raw egg white, confirmed by OFC, compared to the 5-EL, with the same timeframe. This corresponds to an 18-week tolerance acquisition period in the 4-EL group vs. 24 weeks in the 5-EL group.

There is some evidence suggesting that the introduction of baked egg in high-risk children (e.g., those with a history of anaphylaxis) may be both safe and effective (21). However, it remains unclear whether the initial tested dose of baked hen's egg protein in such cases should be lower than, or the same as, that recommended for the general pediatric HEA population.

Therefore, we decided to compare two ladder protocols: the 4-EL, beginning with a muffin containing 1.5 g of hen's egg proteins, and the 5-EL, in which the first two steps consist of muffins containing 0.75 g and 1.5 g of egg proteins, respectively. This approach allows for a reduced allergen load at initial exposure and a longer cumulative exposure to baked hen's egg proteins. Such a strategy may be more appropriate for specific subgroups of patients, particularly those considered to be at higher risk (21).

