### Eligibility criteria

2.4

Eligibility for study participation requires full compliance with all inclusion and exclusion criteria outlined in Table 1 at the time of enrollment.

**Table 1 T1:** Inclusion and exclusion criteria for pediatric patients with hen's egg allergy.

Inclusion criteria	Exclusion criteria
Age ≥12 months and ≤5 years. Diagnosis of IgE-mediated HEA confirmed according to the EAACI guidelines by a positive OFC with hen's egg proteins. In children with high-risk HEA (e.g., history of anaphylaxis), diagnosis can be based on elevated specific IgE levels to hen's egg proteins and/or individual egg components and/or positive skin tests^a^. On a therapeutic elimination diet for at least 6 months, measured from the last allergic reaction to egg (in accordance with BSACI guidelines) (16). Eligible regardless of the risk of systemic reactions (e.g., anaphylaxis) or asthma. Good general health Written informed consent signed by the child's guardians. Demonstrated good cooperation from the patient's guardians.	Confirmed wheat allergy and/or celiac disease. Uncontrolled asthma, defined as the presence of shortness of breath, cough, chest tightness, or auscultatory changes despite treatment. Signs of exacerbation of a chronic disease. Signs of acute infectious disease (e.g., acute rhinitis, cough, subfebrile or febrile states). Exacerbation of another allergic disease (e.g., conjunctivitis, allergic rhinitis, atopic dermatitis). Anaphylaxis due to hen's egg proteins within the last 6 months. Use of antihistamines within 3–10 days before the challenge^b^ (depending on the drug and indication; time-limited contradiction – relative exclusion criterion). Acquired tolerance to baked hen's egg proteins or advancement to a higher step of the egg ladder. Use of immunosuppressive drugs or immunotherapy.

BSACI, British Society for Allergy and Clinical Immunology; EAACI, European Academy of Allergy and Clinical Immunology; HEA, Hen's egg allergy; HEPs, Hen's egg proteins; OFC, oral food challenge.

a Exceptions to the oral food challenge (OFC) protocol may be made for patients presenting with severe anaphylaxis or significantly elevated specific IgE levels (3.5 KU/L) to egg white proteins (designated as a high-risk challenge, where standard protocols contraindicate OFC due to anaphylaxis risk) (7, 21, 22).

b Temporal constraint (relative exclusion criterion).

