### Sequence generation and allocation concealment

2.16

Children will be randomised to either the intervention or control group immediately after enrolment. An independent investigator with no clinical involvement in the trial will generate random assignments using a computer-generated random number table. The random number will be generated in blocked randomization (using the block of 2) with a 1:1 allocation ratio. The randomization will be created using StatsDirect statistical software (Stats-Direct statistical software; http://www.statsdirect.com; England: StatsDirect, 2024).

Allocation concealment will be ensured through the use of opaque, sealed and numbered envelopes. The data regarding intervention assignments will be stored in a sealed envelope in a secure location within the administrative part of the department. An independent person will open the next consecutively numbered envelope and provide the allocation information to the study physician.

Since this is an open-label trial, both the participants and the study team will be aware of the treatment allocation on randomization. In the event of any medical issues, the assigned treatment information will already be accessible to the study physicians and principal researcher, eliminating the need for code-breaking procedures.

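### High-risk status, which motivates the two starting doses, is worded inconsistently in Table 1 and is not a stratification factor, so balance on it is left to chance

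*Protocol article*

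**What the plan says.** Section 2.1 states that for high-risk children "it remains unclear whether the initial tested dose of baked hen's egg protein in such cases should be lower than, or the same as" the amount recommended for the general paediatric egg-allergic population. It then gives this as the reason for comparing the two ladders, adding that "Such a strategy may be more appropriate for specific subgroups of patients, particularly those considered to be at higher risk". The Discussion returns to the same question. The formal primary aim is wider: it compares the ladders "in children diagnosed with IgE-mediated hen's egg protein allergy".

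Table 1 (section 2.4) describes high risk in two places. The inclusion cell reads: "In children with high-risk HEA (e.g., history of anaphylaxis), diagnosis can be based on elevated specific IgE levels", and it also accepts component-specific IgE and/or skin tests. Footnote a, attached to that sentence, allows exceptions to the OFC for "patients presenting with severe anaphylaxis or significantly elevated specific IgE levels (3.5 KU/L) to egg white proteins". Children are eligible whatever their risk of systemic reactions.

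Section 2.16 describes the allocation: "The random number will be generated in blocked randomization (using the block of 2) with a 1:1 allocation ratio". It gives the software and the envelope procedure and names no stratification factor. Section 2.9 sets recruitment at 94 children, 47 per arm.

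**The concern.** The inclusion cell and the footnote answer one practical question: may this child enter without a positive diagnostic OFC? They answer it differently. Take a child with one earlier non-severe anaphylaxis and a mildly raised sIgE. The cell lets this child in without an OFC. Under the footnote the child meets neither condition. In the cell, sIgE is evidence for the diagnosis in a child already called high-risk. In the footnote, sIgE alone can make the challenge high-risk. Recruitment runs in three departments in two cities (section 2.3), so the same child could be handled differently by department.

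Risk status is also a plausible prognostic factor. A positive OFC at any step ends progression (section 2.5.3), so a child who reacts early counts against the primary outcome, and anaphylaxis is itself a secondary outcome. A history of anaphylaxis is available from the screening interview and records (section 2.6), yet the described allocation makes no use of it. Stratification cannot be supplied later by an analysis plan once children have been randomised.

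**Working it through.** **Inputs from the protocol article.** 42 completers per arm, 10% dropout, 47 per arm randomised (2.9); blocks of 2, 1:1 (2.16); 80% vs 69% tolerance in the earlier egg-ladder trial (Introduction).

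**Inputs assumed, because the document gives none.** High-risk share p = 20-40% for imbalance (20-50% for subgroup power); tolerance lower by δ = 20-40 points in high-risk children; overall tolerance 75% where needed.

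**Step 1, the plan's own figure.** 42 / (1 − 0.10) = 46.7, so 47 per arm and 94 in total. This reproduces.

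**Step 2, chance imbalance.** In a block of 2 each arm gets one child. If children arrive independently of risk, a block adds +1 or −1 to the difference in high-risk counts with total probability 2p(1 − p). Over 47 blocks the SD of the difference in proportions is √(2p(1 − p)/47), the same as for two independent binomials.

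| Assumed p | SD of imbalance (points) | P(gap ≥ 5 children) | 1-SD shift, δ = 20 | 1-SD shift, δ = 40 |
|---|---|---|---|---|
| 20% | 8.3 | 0.24 | 1.7 | 3.3 |
| 30% | 9.5 | 0.31 | 1.9 | 3.8 |
| 40% | 10.1 | 0.34 | 2.0 | 4.0 |

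A gap of 5 children is 5/47 = 10.6 points. The shift is SD × δ; for example 0.101 × 40 = 4.0 points. At the edge of the 95% range (1.96 SD, or 16.2 to 19.8 points of imbalance) the shift is 3.2 to 7.9 points.

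**Step 3, comparison with sampling error.** For 80% vs 69% with 47 per arm, SE = √(0.80 × 0.20/47 + 0.69 × 0.31/47) = 8.9 points. The shifts in step 2 are part of this error and do not add to it.

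**Step 4, what stratifying gains.** Relative reduction in SE if risk-related variance is removed: 1 − √(1 − p(1 − p)δ²/(0.75 × 0.25)).
- p = 20%, δ = 20 points: 1 − √(1 − 0.034) = 2%.
- p = 40%, δ = 40 points: 1 − √(1 − 0.205) = 11%.

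**Step 5, can the trial answer for the subgroup?** Shares of 20%, 30% and 50% of the 84 completers give about 8, 12 and 21 high-risk children per arm. Power for 80% vs 69% (two-sided 5%, pooled variance) is 7%, 9% and 12%. For an arm-by-risk interaction at 69% tolerance, SE = √(0.69 × 0.31 × (2/n_high + 2/n_low)), with n_low = 34, 30 and 21. The interaction detectable with 80% power is about 72, 63 and 57 points. Stratifying does not materially change this.

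**The case against.** The strongest case against runs as follows. The inclusion cell offers an example, not a definition, and the footnote qualifies the same sentence, so these are not two definitions that exclude each other. In particular, a child with high sIgE and no anaphylaxis is not shut out by an example. The word elevated already gives the direction of the sIgE condition. The stated aim covers all children with IgE-mediated egg allergy, the remark about higher-risk children is hedged, and section 2.9 calls the trial a pilot. Stratification is optional, and 1:1 randomisation balances risk in expectation.

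Most of this stands, and it rules out two stronger readings.

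- A reader might infer that the trial cannot balance risk status. It can and does in expectation. What is missing is assurance of balance in the realised sample, and the planned confidence intervals already allow for chance imbalance.
- A reader might infer that missing stratification is why the high-risk question cannot be answered. Step 5 shows that sample size is the limit. Nor is the absence of a risk-subgroup analysis from the article a fault, since an analysis plan not shown may contain one.

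The document also does not say that risk status is the strongest predictor of a failed challenge. Section 2.6.3 discusses the sIgE/total IgE ratio and the basophil activation test as predictors.

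What survives is the difference between any and severe anaphylaxis, the change in the role of sIgE from evidence to criterion, the missing inequality sign, and an allocation that does not use a factor the protocol itself treats as important.

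**Conclusion.** The point holds as an inexpensive improvement, not as a flaw that invalidates the comparison. Table 1 gives inconsistent, non-operational conditions for entry without a diagnostic OFC, and the passages must be reconciled. The described allocation leaves balance on risk to chance. Under the assumed share and effect, a typical imbalance is worth about 2-4 points against an SE of about 9, and stratifying would shorten the SE by roughly 2-11%. The gain is modest and rests on inputs the document does not give. The inconsistency in Table 1 rests on the text alone.

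**What to change.** 1. Reconcile the Table 1 inclusion cell and footnote a into one operational high-risk criterion: which anaphylaxis history counts, and which sIgE, with the inequality stated. The clinical threshold is for the investigators to set.
2. Record the status on the case report form before the envelope is opened.
3. Stratify the allocation list by it, with a separate envelope series per stratum, and take account of the stratum in the analysis so that the precision is realised. For children already randomised, adjust for risk status instead.
4. Present any results by risk stratum as exploratory, since an assumed 8-21 high-risk children per arm cannot give a firm answer.

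Cost: one table edit, one field on the form, and a second envelope series for each list. Incomplete blocks may leave the arms unequal by a child or two, and risk status must be settled before allocation.

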### Study design

2.2

To compare both treatment strategies, we will conduct a multicenter, open-label, randomized superiority trial with two parallel arms and a 1:1 allocation ratio.

### Study setting

2.3

Participants will be recruited, and the intervention will be implemented at two departments of the Medical University of Warsaw: the Department of Paediatrics and the Department of Paediatric Pneumonology and Allergology, as well as at the Department of Pediatrics and Allergy at the Medical University of Lodz (academic hospitals). All centers have substantial expertise in the management of pediatric food allergies, particularly in conducting oral food challenges (OFCs). In addition, the research team has extensive experience in the design and implementation of clinical trials. Participant recruitment is scheduled to begin in July 2025 and is expected to be completed within 36 months. Investigators will regularly review lists of potentially eligible patients with IgE-mediated HEA. Other team members will also be informed about study design and eligibility criteria to refer potential participants.

### Eligibility criteria

2.4

Eligibility for study participation requires full compliance with all inclusion and exclusion criteria outlined in Table 1 at the time of enrollment.

**Table 1 T1:** Inclusion and exclusion criteria for pediatric patients with hen's egg allergy.

Inclusion criteria	Exclusion criteria
Age ≥12 months and ≤5 years. Diagnosis of IgE-mediated HEA confirmed according to the EAACI guidelines by a positive OFC with hen's egg proteins. In children with high-risk HEA (e.g., history of anaphylaxis), diagnosis can be based on elevated specific IgE levels to hen's egg proteins and/or individual egg components and/or positive skin tests^a^. On a therapeutic elimination diet for at least 6 months, measured from the last allergic reaction to egg (in accordance with BSACI guidelines) (16). Eligible regardless of the risk of systemic reactions (e.g., anaphylaxis) or asthma. Good general health Written informed consent signed by the child's guardians. Demonstrated good cooperation from the patient's guardians.	Confirmed wheat allergy and/or celiac disease. Uncontrolled asthma, defined as the presence of shortness of breath, cough, chest tightness, or auscultatory changes despite treatment. Signs of exacerbation of a chronic disease. Signs of acute infectious disease (e.g., acute rhinitis, cough, subfebrile or febrile states). Exacerbation of another allergic disease (e.g., conjunctivitis, allergic rhinitis, atopic dermatitis). Anaphylaxis due to hen's egg proteins within the last 6 months. Use of antihistamines within 3–10 days before the challenge^b^ (depending on the drug and indication; time-limited contradiction – relative exclusion criterion). Acquired tolerance to baked hen's egg proteins or advancement to a higher step of the egg ladder. Use of immunosuppressive drugs or immunotherapy.

BSACI, British Society for Allergy and Clinical Immunology; EAACI, European Academy of Allergy and Clinical Immunology; HEA, Hen's egg allergy; HEPs, Hen's egg proteins; OFC, oral food challenge.

a Exceptions to the oral food challenge (OFC) protocol may be made for patients presenting with severe anaphylaxis or significantly elevated specific IgE levels (3.5 KU/L) to egg white proteins (designated as a high-risk challenge, where standard protocols contraindicate OFC due to anaphylaxis risk) (7, 21, 22).

b Temporal constraint (relative exclusion criterion).

Given that some studies have reported higher allergenicity of baked egg products prepared with non-wheat based batters compared to those with wheat-based batters, children with wheat allergy or celiac disease requiring wheat flour substitution will be excluded from participation (10).

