## Introduction

1

Hen's egg allergy (HEA) is one of the most common food allergies affecting the pediatric population, with an incidence of HEA of less than 1.2% in children under 2 years of age (1, 2). The standard of care for HEA is an elimination diet excluding hen's egg proteins. However, this approach, especially when followed long-term, presents several challenges, including delayed introduction of complementary foods, malnutrition, impaired growth, feeding difficulties and even social exclusion (3, 4).

Available evidence suggests that spontaneous resolution of HEA occurs in the majority of affected children over time. In the *EuroPrevall* study, 49% of children with HEA (*n* = 24/49) achieved tolerance to hen's egg proteins one year after diagnosis (1). Additionally, in the Australian *HealthNuts* cohort study, HEA resolved in 89% of participants (*n* = 287/323) by the age of 6 years (5). Nonetheless, a gradual reintroduction of heated egg using the egg ladder (EL) approach may accelerate the time to tolerance acquisition (6).

The egg ladder involves the gradual introduction of egg, beginning with less allergenic, extensively heated forms in small amounts, and progressing to lightly-cooked egg in regular, age-appropriate portions (7). The rationale for using the EL to assess tolerance acquisition is based on the lower allergenicity of baked compared to its unheated form. This reduction in allergenicity is attributed to the degradation of conformational IgE-binding epitopes caused by high-heat exposure (e.g., baking in the oven at 180°C for 30 min), as well as the “matrix effect” of the wheat-based batter – both shown to reduce IgE antibody binding to egg white proteins, thereby attenuating their allergenicity (8–10).

Leonard et al. demonstrated that the regular dietary inclusion of baked egg (e.g., a muffin or waffle containing 3.3 g of hen's egg proteins) reduced the time to tolerance induction to 50 months, compared to 78 months in children adhering to a strict egg avoidance diet (11). A 2025 systematic review summarized that in most studies, baked egg is safe and well-tolerated, with overall tolerance rates among children with HEA ranging from 70% to 97% (8, 9, 12). Furthermore, a 2024 systematic review and meta-analysis of 8 studies reported that 69% of children with HEA achieved tolerance to raw egg using the EL (95% CI: 0.5–0.85; *n* = 193) (8).

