#### Primary outcome

2.11.1

The primary outcome is the percentage of children who acquire tolerance to soft-boiled hen's egg (almost raw hen's egg proteins), as determined by a negative OFC at the final step of the EL. Soft-boiled egg will be administered at the end of the observation period (18 or 24 weeks, depending on the assigned study arm).

The challenge dose will consist of 0.5–1 egg for children aged 1–3 years and 1 egg for those aged 4–5 years, corresponding to a maximum total of 6 g of hen's egg proteins. The outcome will be reported as a difference between two study arms.

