This rigorously designed RCT will help to compare the efficacy of two ladders: the 4-EL which begins with a higher amount of baked hen's egg proteins (1.5 g), and the 5-EL, in which gradual reintroduction starts with two steps – muffins containing 0.75 g and 1.5 g of egg proteins, respectively. Currently, it is unclear whether the initial reintroduced dose of baked hen's egg protein in children with IgE-mediated HEA, especially those in high-risk groups, should differ from that used in children with mild and moderate non-IgE mediated HEA. This study will be conducted by a research center experienced in RCTs involving children and food allergy. The study team is supported by [name], who serves as a scientific mentor and provides expert oversight in protocol development and clinical decision-making in complex cases. The findings of this RCT will address current evidence gaps and inform guideline development groups regarding the efficacy and safety of the 4-EL in children with IgE-mediated HEA.

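### No challenge confirms current egg allergy before randomisation, so children who had already outgrown it are scored as having acquired tolerance; arm-level rates cannot be read as ladder efficacy

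*Protocol article*

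**What the plan says.** Section 2.4 (Table 1) of the protocol article requires "Diagnosis of IgE-mediated HEA confirmed according to the EAACI guidelines by a positive OFC with hen's egg proteins" but sets no date window for that challenge. For high-risk children "diagnosis can be based on elevated specific IgE levels to hen's egg proteins and/or individual egg components and/or positive skin tests". All children must also be "On a therapeutic elimination diet for at least 6 months, measured from the last allergic reaction to egg", which is a minimum with no maximum. The one related safeguard is the exclusion for "Acquired tolerance to baked hen's egg proteins or advancement to a higher step of the egg ladder".

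Section 2.6 describes screening as an interview, a physical examination and a review of records. The first study challenge is the step-1 muffin, given after randomisation, and soft-boiled egg is first given at the last step. Under section 2.5.3, all children with a positive OFC leave the study.

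Section 2.11.1 defines the primary outcome as "the percentage of children who acquire tolerance to soft-boiled hen's egg", judged by a negative OFC at the final step. Section 2.1 calls the 18 and 24 weeks a tolerance acquisition period. The Introduction reports that 49% of children in one cohort (24/49) "achieved tolerance to hen's egg proteins one year after diagnosis", and that 89% (287/323) in another had resolved by age 6. The closing sentence of the Discussion says the trial will inform guideline groups "regarding the efficacy and safety of the 4-EL in children with IgE-mediated HEA".

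**The concern.** To acquire tolerance a child must be reactive at the start. The plan verifies this only through past evidence. A positive OFC is itself an allergic reaction, so the 6-month rule normally makes the qualifying challenge at least 6 months old, and it may be much older. A child who outgrew the allergy during the elimination period will pass every step and be credited to the ladder. Because a positive study OFC ends participation, no child counted as a success ever has reactivity documented within the trial.

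Two things are at stake. First, each arm's tolerance rate mixes resolution before the first muffin with whatever the ladder does, and no elimination-diet arm exists to separate the two. Secondly, if the ladders differ only in children who are still allergic, the already resolved children reduce the observed difference in a superiority trial that is also meant to supply effect sizes for later trials.

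**Working it through.** **The plan's own figure.** Section 2.9 recruits 94 (47 per arm) to keep 84 (42 per arm) after 10% dropout: 84/0.9 = 93.3, rounded up to 94; 42/0.9 = 46.7, rounded up to 47. This reproduces. The plan gives no share of children already resolved at entry, so that has to be approximated.

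**Inputs.** 24/49 = 49% tolerant one year after diagnosis (Introduction); minimum gap of 6 months since the last reaction (Table 1); 47 children per arm (section 2.9).

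**Assumptions.** Resolution follows a constant hazard, and the cohort's clock from diagnosis can be applied to time since the last reaction in this population. The documents support neither assumption directly.

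**Share already resolved at entry.** r(t) = 1 − 0.51^(t/12), with t in months.
- t = 6: 1 − 0.51^0.5 = 1 − 0.714 = 28.6%, or 47 × 0.286 = 13.4 children per arm.
- t = 12: 49%, by construction.

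**Sampling uncertainty in 24/49.** The Wilson 95% interval, (p + z²/2n ± z√(p(1−p)/n + z²/4n²))/(1 + z²/n) with p = 0.490, n = 49 and z = 1.96, is 35.6% to 62.5%. At 6 months:
- lower: 1 − (1 − 0.356)^0.5 = 19.7%, or 9.3 of 47;
- upper: 1 − (1 − 0.625)^0.5 = 38.8%, or 18.2 of 47.

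**Cross-check with the second cohort.** If the 89% by age 6 is spread over 5 years at a constant hazard (assumed), 1 − 0.11^(6/60) = 19.8% at 6 months. This sits at the lower end of the range above.

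**Effect on the comparison.** If a share r in each arm is already resolved and passes every OFC, an arm's success rate is r + (1 − r)p, where p is the rate among still-allergic children. The between-arm difference is then (1 − r)(p₁ − p₂). Randomisation gives both arms the same r in expectation, so the contrast is a valid estimate for the children enrolled, but smaller than the contrast among still-allergic children whenever r > 0. Neither r nor p₁ − p₂ can be taken from the documents.

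**Chance imbalance.** At r = 0.286 with 47 per arm, the standard deviation of the between-arm difference in r is √(2 × 0.286 × 0.714/47) = 0.093, about 9 percentage points. This is part of ordinary sampling error. Baseline covariates related to resolution could remove some of it.

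**The case against.** The strongest reply is that the trial's inference is comparative. Section 2.11.1 reports a difference between arms, and section 2.11.2 says the same of all secondary outcomes. Randomisation balances resolved children in expectation. A reader might infer that the between-arm result is biased. It is not, and this part of the reply stands.

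It can also be argued that silently resolved children belong to the target population. Table 1 attributes the 6-month rule to a guideline, and section 2.1 asks whether the 4-EL is sufficient for assessing tolerance. On that reading the contrast in the enrolled population is the wanted effect. That is a legitimate estimand, but it fits badly with the word acquire in section 2.11.1 and with conclusions about the 4-EL that name no comparator.

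A reader might also multiply the 80% v. 69% quoted in the Introduction by (1 − r) to put a number on the lost effect. The documents do not support this. Those rates come from a trial in children who already tolerated baked egg, a group that Table 1 excludes, under 18- and 30-month protocols. Nothing shows that the rates leave out spontaneous resolvers.

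The resolved share is also uncertain in both directions. Excluding children known to tolerate baked egg and admitting high-risk children would lower it; long gaps since the last reaction would raise it. "Eligibility for study participation requires full compliance with all inclusion and exclusion criteria outlined in Table 1 at the time of enrollment" might be read as a guarantee of current allergy, but no described procedure would detect unrecognised tolerance. The contact 6 weeks after the ladder (section 2.8) checks that tolerance persists and says nothing about the state at entry.

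Finally, covariate models often belong to an SAP. Here, section 2.19 already names unadjusted tests with RR and NNT, so the choice can be commented on.

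**Conclusion.** The point holds as one about interpretation and precision. Nothing in the article establishes current clinical reactivity at randomisation, and the outcome wording credits the ladder with resolution that may have come before it. Under a constant hazard and transfer of the cited cohort, about 29% of children would already be resolved at the 6-month minimum, with about 20% to 39% reflecting sampling error in 24/49 alone. The true share is unknown and could lie outside that range.

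The comparison of 4-EL with 5-EL remains valid for the enrolled children. Arm-level tolerance rates cannot be presented as efficacy of either ladder. A difference confined to still-allergic children would be diluted by the factor (1 − r), which the documents do not allow to be fixed. The limitations listed in the Discussion do not mention any of this.

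**What to change.** 1. In section 2.11.1 and the abstract, state the primary outcome as the proportion tolerant to soft-boiled egg at the final OFC. The abstract at present describes it in terms of raw egg.
2. In the Discussion part of the abstract and the closing paragraph of section 3, limit conclusions to 4-EL relative to 5-EL, and state that each arm's rate includes spontaneous resolution.
3. In section 2.19, replace the unadjusted primary comparison with a prespecified risk difference (or RR) adjusted for baseline egg-white sIgE on the log scale and for months since the last reaction or positive OFC. Keep the unadjusted test as supportive. The sIgE is already drawn before the first OFC (section 2.6.3), and the date is already needed to check eligibility.

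The adjustment does not identify resolved children. It uses information related to resolution to reduce noise and chance imbalance. Restricting a sensitivity analysis to children whose last reaction was within 12 months would not solve the problem: under the same assumed hazard, 29% to 49% of children with gaps of 6 to 12 months are already resolved.

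The cost is slightly more analysis work and a less favourable efficacy statement. No challenge, visit or patient is added, and no clinical rule changes.
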